#### Associated clinical rehabilitation

In order not to undermine optimal recovery potential and since we are testing an innovative tDCS protocol for which clinical efficacy is not warranted, all participants will be enrolled in parallel, in a similar “live” on-site rehabilitation program. Stimulation sessions will be conducted in the morning (8–12 am) and “live” rehabilitation sessions delivered independently in the same institution will follow. Rehabilitation activities during participation in the trial aim to maximize the chances of optimal recovery given the uncertain therapeutic value of our intervention and were specifically requested by our local Institutional Review Board for ethical reasons.

The on-site “live” program is based on an intense multidisciplinary rehabilitation plan encompassing specific goal-directed qualitative interventions, combining physical therapy, occupational therapy, neuropsychological, and speech therapy interventions, with a duration and periodicity of 1 to 2.5 hours a day, 2–3 days a week. Hence, all participants will conduct equivalent rehabilitation activities based on identical goal-directed qualitative occupational principles. On stimulation days, when hospital rehabilitation cannot be performed live on-site, participants will be instructed to carry out 1–2 hours of rehabilitation at home based on the same activities usually performed in the hospital. Clinical physical therapy is mainly focused on gross motor functions and postural control training (i.e., reaching, straightening, and support abilities), somatosensory integration, and gait rehabilitation. Occupational therapy exercise upper limb fine motor function, spasticity reduction, manual skill training, and multisensory stimulation. Finally, neuropsychological rehabilitation is mainly centered on training executive function and the management of emotions (i.e., impulsivity, liability, childish behavior, apathy, orientation and depression).

#### Safety monitoring

No major side effects of stimulation or the follow-up of stroke patients are to be expected given the well-known safety profile of tDCS interventions in neuropsychiatric patients. Nonetheless, in order to monitor safety and to evaluate tolerance and comfort to tDCS, participants will complete before and immediately following each stimulation session, a standardized adverse effect questionnaire [10] documenting the incidence and intensity of the most common side effects of tDCS stimulation (notably itching, pain, burning, fatigue and headache). Even if extremely unlikely, in case of a major adverse event-related or unrelated to stimulation such as for example a second stroke or an epileptic seizure participants will cease participation in the study and will be immediately provided with medical assistance and follow-up care in our institution.

### Outcome measures

In agreement with our objectives, the primary outcome measure (addressing the main and key objective) of our trial will evaluate changes in the Fulg-Meyer Assessment (FMA) for the impaired upper limb. A set of secondary outcome measures recorded prior to and following tDCS treatment (addressing study objectives 2, 3, and 4) will assess respectively: (2.1) Patient’s performance in a series of computer-based behavioral tasks evaluating visuo-motor adaptation (anterior cerebellar lobe contributions) and also sustained attention and cognitive control (prefrontal contributions); (2.2) Changes in resting-state and task-evoked EEG recordings and (2.3) set of clinical scales evaluating global stroke severity, cognitive impairment and their recovery, and correlations with predicted electric field distribution model features and stroke lesion hallmarks revealed by structural MRI neuroimaging. Find below a detailed explanation of the different outcome measures employed in our study.

#### Fugl-Meyer Assessment (FMA)

Addressing the primary or key goal of our study, the Fugl-Meyer Assessment (FMA) will be used to evaluate upper limb motor improvements. This is a widely employed tool used to assess motor impairment in post-stroke participants and considered one of the most comprehensive and reliable quantitative measures for motor hemiplegic dysfunction [46]. Among the sub-sections of this assessment we will focus on evaluating the upper limb/extremity motor domain (FMA-UE). Even so, the lower limb/extremity section of the assessment (FMA-LE) will be also administrated to evaluate the status and changes in lower limb motor function. The FMA-UE and FMA-LE include a series of items measuring movement, coordination and reflexes, each one scored on a 3-point ordinal scale (0 = cannot perform, 1 = performs partially, 2 = performs fully), with a total score of 0 points equaling absolute hemiplegia, and 100 points signalling sound motor function; of these 100 points, 66 are attributed to the upper extremity (FMA-UE) and 34 to the lower extremity (FMA-LE). For intra-subject pre-post-intervention assessments, an improvement greater than 6 points is usually defined as clinically significant.

#### Visuo-motor adaptation task

A visuo-motor adaptation task known to assess contributions from the anterior cerebellar lobe to voluntary motor function [47–50] programmed in a MATLAB environment (R2019a, Mathworks, USA) and Psycho-Toolbox will be implemented. During the task, participants will seat in a comfortable chair in an isolated room with no distractions at a distance of 57 cm (arm’s reach) in front of a 15-inch computer monitor, holding a hand-joystick with their impaired paretic upper limb. Hand splints to ensure correct attachment to the joystick will be employed if necessary for all subsequent measures to keep conditions constant. During the task, the joystick position will be displayed as a red dot of 1-cm diameter. Participants will be asked to complete a series of consecutive trials to direct the cursor (a red dot) from the center of the screen (starting point) towards the interior of a randomly allocated peripheral target displayed as a green circle. Each trial will start with the green circle and the red dot in the center of the screen. Subsequently, additional green circles (targets) will appear randomly in 4 possible locations, equally spaced around a virtual circle respecting a homogeneous 5 cm distance from the starting point. Participants will have 10 secs to move the red dot and place it inside the circle and maintain such position for 0.5 s. Once completed, the green circle will jump back to the starting point, and  participants had to replace the dot in the starting position to complete the trial. During the inter-trial interval (1.5 secs), a full gray screen with a center stimulus (“ + ”) will be displayed to keep participants alert and ready for a subsequent trial. If the trial is not successfully completed, hence the participant does not succeed in placing the dot inside the circle during the allotted time window, the circle will automatically jump to the starting point. Visual feedback of the dot and the circles will be displayed in real time (see Fig. 4A). The task will be divided into 2 consecutive blocks. The first block (familiarization) will consist of 32 trials, and will be followed by a second block (motor adaptation)including 64 trials. During the familiarization block, trials will be conducted as previously described. During the motor adaptation block, a “force-field-like” perturbation will be implemented by introducing a constant 45° angular rotation between the trajectory of the red dot trajectory and the real movement of the joystick, deviating the trajectory of the former and forcing participants to compensate for such shifts in order to reach the target in the alloted time, hence engaging visuo-motor adaptation (learning) skills.

**Fig. 4 Fig4:**
[figure not shown]
Computer-based selected tasks to assess cerebellar (motor learning and adaptation) and dorsolateral prefrontal (sustained attention and cognitive control) contributions to motor functions and their changes following stimulation. **A** Visuo-motor adaptation experimental paradigm design and setup. Following a stimulus (“ + ”), a red cursor representing the joystick position is displayed in the center of a computer screen. Participants are required to direct the cursor moving the joystick towards a randomly allocated target (within a time window of 10 secs) displayed as a green circle among other targets, equally spaced around a virtual circle. In the motor adaptation block, a force field with a 45° constant perturbation is applied deviating the trajectory of the cursor respect the actual joystick trajectory, hence forcing the participant to adapt and learn how to compensate such a deviation. **B** AX-CPT experimental design. Participants are instructed to attend to serial presentation of letters and to make a target response each time the correct 'cue-probe' (A + X) combination is presented (by pressing the key “1” on a keyboard), or execute an alternative response (by pressig the key “z”) for all other incorrect 'cue-probe' combinations (e.g., A + S, M + X). During the experimental recording, a total of 150 trials encompassing the presentation of a cue stimulus (1000 ms), a fixation stimulus “ + ” (1000 ms), and a probe stimulus (1000 ms) followed by an inter-trial interval (1500 ms) are completed. ITI: Inter-trial Interval

#### AX continuous performance task

The AX continuous performance task (AX-CPT) is a computer-based paradigm running in E-prime software (E-Prime®, Psychology Software Tools, Sharpsburg, PA, USA) which has been extensively used to explore DLPFC contributions to sustained attention and cognitive control subtended by prefrontal systems. Moreover, performance in the task has been correlated with the severity of the motor impairment [51–53]. In this paradigm, participants will be comfortably seated at a distance of 57 cm from a 15-inch computer screen in an isolated room with no distractions, and required to attend to a serial presentation of letters and provide a response (press the “Q” key on the keyboard) every time the cue-probe letter combination “A” + “X” is presented. Likewise, participants are also instructed to execute an alternative response (press the “Z” key) when any cue-probe letter combination other than “A” + “X” is displayed on the screen (e.g., “A” + “S”). Participants are required to respond as quickly and accurately as possible after each cue-probe combination during a response interval using their non-impaired hand (please see Fig. 4B). Each trial consists of a cue letter stimulus (1000 ms duration), the “ + ” fixation stimulus (1000 ms duration), and a probe letter stimulus (1000 ms duration) followed by a 1500-ms response interval displaying a white screen. Letters on the screen will always be displayed in Times font (40 size), in black capital letters on a white background. The task will be split into two parts: first, (1) a series of practice trials acclimating the participant to the paradigm while receiving the researcher’s constant feedback to ensure participants correctly understand the task; second, (2) the experimental trials will be launched after a short rest (duration determine ad libitum by subject preferences). Twelve trials will be presented during a practice block followed by an experimental block including a total of 150 trials. Responses in both the practice and the experimental blocks will be recorded, but only the latter will be used for statistical analyses.

#### EEG acquisition

EEG data will be recorded with the same HD-tDCS equipment used for stimulation, a Starstim® 8 channel device controlled by the Neuroelectrics Instrument Controller® software (Neuroelectrics, Barcelona, Spain) able to sample scalp EEG signals at a frequency of 500 Hz using scalp NG pistim® electrodes ($${\mathrm{\pi cm}}^{2}$$ Ag/AgCl) and SignaGel® (Parker laboratories, USA). Skin/electrode impedance values will be automatically monitored and kept at all times below 5 KΩ. The 8 recording electrodes will be distributed across left and right hemi scalp positions (F3, F4, C3, C4, P3, P4, PO10, and PO9) according to the 10/20 EEG system, to capture among other sources, derived EEG activity associated to prefronto-central, and fronto-parietal motor/premotor networks. All EEG sessions will be conducted under the same conditions with a combined ground reference placed in the right earlobe. Ten minutes of resting-state EEG data (eyes open fixating on a target located at arm’s reach, ~ 57 cm) will be acquired during the baseline assessment, the post-stimulation regime assessment, and during the follow-up visit. EEG will be also continuously recorded during our visuo-motor adaptation task assessing cerebellar contributions to motor learning and during the AX-CPT paradigm assessing dorsolateral prefrontal contributions to sustained attention and cognitive control. Finally, 5 min of continuous resting-state EEG data (eyes open) will also be recorded prior to and following each of the 10 sessions of tDCS stimulation.

#### National institutes of health stroke scale

The National Institutes of Health Stroke Scale (NIHSS) is a quantitative scale of stroke-related neurologic deficits widely used to characterize baseline impairment in clinical trials [54]. It explores consciousness level, visual field surface, language function, the presence of hemineglect, hemiplegia, movement disorders, and impairments of sensory function. It consists of 15 items, each one scored from 0 to 4, to reach a total of 42 potential points, in which higher scores signal more severe impairment (0 = no stroke symptoms, 1–4 = minor impairment, 5–15 = moderate impairment, 16–20 = moderate to severe impairment, 21–42 = severe impairment). We will use the NIHSS to characterize the stroke severity of our patients and also use it to verify the comparability of each of the 4 experimental tDCS groups defined in our trial.

#### The Montreal cognitive assessment

The Montreal Cognitive Assessment (MoCA) is a quantitative screening tool used to explore stroke-related cognitive deficits [55]. It is made of a series of questions and tasks specifically designed to assess visuo-spatial and executive function, working memory, short-term memory, sustained attention, abstraction, language, and orientation in time and space. It contains a total of 10 items, for a total of 30 points, and lower scores indicate  higher levels of impairment (26–30 = no stroke cognitive impairment, 18–25 = mild cognitive impairment, 10–17 = moderate cognitive impairment, 0–10 = severe cognitive impairment). We will use the MoCA to evaluate participants’ cognitive impairment/improvement and also to asses group comparability.

#### Screening of hemispatial neglect

In order to monitor the presence of hemispatial neglect, participants will conduct a letter cancellation test, a Bells cancellation test, and a line bisection test. The letter cancellation test quantifies the presence of visuo-spatial  neglect and visual search/scanning deficits [56]. In the task, a total of *n* letters is distributed into 6 lines presented in paper format. Among them, the letter “H” is repeated 104 times. Participants will be asked to visually screen the paper sheet and find and outline as many letters “H” as they can find. The Bells cancellation test quantifies visual neglect deficits in the extra personal space [57]. A total of 35 bells are embedded within 280 distractors presented in paper format. Participants will be instructed to circle or cancel off all drawings corresponding to bells. All stimuli are of the same size and displayed in black color over a white background. Though they might appear randomly distributed, bells are presented in 7 columns; 3 columns on the left and the right hemifields and one in the middle, with 5 bells and 40 distractors on each one. The sheet of paper with the test display will be placed right in the middle of the visual field and the participant is free to explore the document with his/her gaze. Finally, the line bisection test identifies and quantifies visuo-spatial orienting impairments and spatial neglect deficits [58]. In this task, several examples of two types of black lines, 5 and 10 cm long, are presented on a white paper sheet placed in the middle of the participant’s visual field. Participants, who are free to explore stimuli with their  gaze, are instructed to identify the center of each horizontal line and bisect it with a pencil.

#### MRI imaging acquisition

MRI structural scans will be obtained from all stroke patients. These will be either drawn in anonymized coded form from recent recordings stored as clinical records by an authorized neurologist working for the protocol, or if not available, acquired  de novo within the 2 weeks before tDCS treatment onset. A 3-Tesla MRI scanner (Siemens Healthcare, Germany) located at the neuroradiology department at Hospital Universitari Joan XXIII in Tarragona will be used for image acquisition. In that case, a T1-weighted 3D anatomical sequence will be carried out  with the following parameters: repetition time = 2500 ms, echo-time = 2.12 ms, number of slices = 156, slice thickness = 0.94 mm, matrix size = 232 × 288, in-plane resolution = 0.83 mm × 0.83 mm, and flip angle = 9 °.

#### Data collection and management

All data generated by the study will be hosted in a secured internal server, property of the *Universitat Rovira i Virgili* (URV) in Tarragona. A shared encrypted database allowing access to anonymized datasets only to authorized co-investigators with a valid personal ID has been set up.Our clinical trial will generate three large classes of records: (1) demographic information, (2) clinical outcome datasets, and (3) neuroimaging and electrophysiological datasets including MRI scans and EEG recordings. Two computers, property of the URV, secured with personal encrypted passwords, will be used for databasing. Given the volume and complexity of the pre-processing involved in the analysis of MRI and EEG datasets, these datasets will be stored in specific computers handled by expert investigators associated to the project. To ensure data quality, all co-investigators and associated personnel taking part in the E-Brain trial will be trained by the principal investigators (co-authors [name], [name], and [name]) to perform any of its procedures (screening, recruitment, informed consent, randomization and allocation, blinding, cognitive and clinical evaluations, EEG/MRI recordings, and tDCS application) by following strictly the conditions, criteria, materials, and methods established in the written protocol approved by our local IRB. In the same vein, all data will be collected by the same institution, and co-investigators will be specifically trained to strictly respect and implement established protocols for data collection, anonymization, storage, analytical strategies and “cloud” data management. To maintain at all times data anonymity and confidentiality, a reference number representing the participant until the study is terminated identifying individual datasets in our databases will be assigned to each participant at inclusion. Only co-authors [name], [name], and [name] will be provided access to the full dataset generated by the study, with the exception of group allocation information which, as stated previously, will only be unblinded to these investigators, once data collection and analyses are completed.

## Data analyses

### Analysis of clinical and cognitive performance outcome measures

Outcomes extracted from computer-based tasks and clinical scores (see the previous section) will be analyzed to explore the differential ability of active tDCS conditions compared to sham stimulation to induce upper limb motor recovery following a stroke. For the clinical tests (FMA, NIHSS, MoCA, and hemispatial neglect tests), mean group scores post vs. pre-tDCS baseline intervention,and during the follow-up assessment, will be compared across experimental groups. Sociodemographic data will also be compared between treatment groups (Group 1: ipsi-DLPFC, Group 2: contra-CEREB, Group 3: ipsi-DLPFC + contra-CEREB, Group 4: SHAM) to identify potential collapse factors.

In order to quantify changes in motor performance with the visuo-motor adaptation task,and assess tDCS effects applied over the cerebellum or the dorsolateral prefrontal areas on upper limb voluntary motion, the following set of measures will be used: (i) the angular trajectory error (“SumErr”; cm) estimating accuracy, consisting of the sum of observed deviations from the ideal linear trajectory at peak tangential velocity (PV)for each trial of the motor adaptation block; (ii) the area under the learning curve (AUC) measuring patients’ adaptation rate,calculated by performing a power fit on the mean learning values of each participant; (iii) the coefficient of variation (CV)measuring the variability of motor performance during the adaptation plateau phase (i.e., when the AUC is stabilized and reaches stable levels) and calculated as the standard deviation (SD) divided by the mean over trials belonging to the plateau phase (AUC/Time-to-target). All these metrics will be represented in ordinal and mean group scores for post vs. pre-tDCS baseline intervention, and for the follow-up milestone and compared across tDCS groups.

In order to quantify sustained attentional abilities (as a proxy of dorsolateral prefrontal  modulation by tDCS) with the AX-CPT task, we will analyse the total number of errors used as a proxy of sustained attention failure. An ordinal value will be taken and group means will be compared between pre- vs. post-tDCS  and for the follow-up milestone. In order to indentify and quantify changes of visuo-spatial performance (as a proxy of visuo-spatial orienting and selective attentional disability), the number of  crossed/circled letters (letter cancellation test) or bells (Bells cancellation test) and the shift (in mm and % of the total line length) of manual bisections from the precise midpoint of each line (line bisection test) will be analysed. Mean group total ordinal scores will be compared between groups acrossthe different time points (pre-, post-tDCS s and follow-up milestones). Other unanticipated complementary metrics could also be taken into account for the final analyses.

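### The learning-curve AUC is labelled an adaptation rate but mixes rate with general arm error, and no listed metric uses the unperturbed familiarisation trials as a reference

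*Protocol article*

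**What the plan says.** The task is described in the protocol article under Visuo-motor adaptation task. Patients perform it "holding a hand-joystick with their impaired paretic upper limb". "The first block (familiarization) will consist of 32 trials", without perturbation. A block of 64 trials follows, with a constant 45° rotation between joystick and cursor and targets 5 cm from the start.

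The metrics are in the section Analysis of clinical and cognitive performance outcome measures:

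- SumErr is introduced as "the angular trajectory error (“SumErr”; cm) estimating accuracy", "consisting of the sum of observed deviations from the ideal linear trajectory at peak tangential velocity", and is taken "for each trial of the motor adaptation block".
- The second metric is "the area under the learning curve (AUC) measuring patients’ adaptation rate", "calculated by performing a power fit on the mean learning values of each participant".
- A coefficient of variation over the plateau phase measures variability.

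Each metric is compared across groups for post against pre and at follow-up. None is said to use the familiarisation block, and no baseline term is named in the power fit. The article then says that further, unanticipated metrics may be considered, but specifies none.

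Two other places rely on the task. Secondary objective 2 (Study objectives) treats motor adaptation as the process sensitive to cerebellar stimulation. The Discussion says that the tasks will serve to verify that motor gains are mediated by modulation of the targeted networks.

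**The concern.** An area under an error curve is a total, not a rate. It falls when a patient adapts faster, but also when the whole curve moves down. With a paretic limb, part of the error on every trial is ordinary execution error that would be present without any rotation. Improving control of that limb is the aim of the trial.

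If an active arm improves general control, its AUC and SumErr will fall relative to sham although patients adapt no faster. Under the AUC's label, that fall would read as better cerebellar adaptation. The planned correlations between task outcomes and FMA would partly reflect the same shared arm control. The 32 unperturbed trials measure that component at each visit, but the listed metrics leave them out.

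**Working it through.** The article gives no figure for these metrics, so there is nothing to reproduce. The check is how AUC behaves under a simple curve.

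**Inputs from the article:** 64 perturbed trials, 32 unperturbed trials, a power fit, 45° rotation, 5 cm target distance.

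**Assumed inputs (the article gives none):** error on trial t is E(t) = c + a × t^(-b). Here a is the initial error due to the rotation, b the adaptation rate, and c the execution error also present without rotation. Ranges: a = 2 to 4 cm, b = 0.1 to 0.5, c = 0 to 1.5 cm. For scale, an uncorrected 45° rotation over 5 cm gives 5 × sin 45° = 3.5 cm perpendicular deviation, or 2 × 5 × sin 22.5° = 3.8 cm between end points.

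**Step 1: AUC scales with level.** With c = 0, the area from t = 1 to 64 is a × (64^(1-b) − 1)/(1 − b), which is proportional to a for any b. At b = 0.3, 64^0.7 = 18.38, so the area is a × 17.38/0.7 = 24.83a. That gives 49.7 for a = 2 and 99.3 for a = 4: a twofold gap at one rate. The results below use the trapezoid rule over the 64 trials, which differs from the formula by about 0.1.

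**Step 2: AUC also responds to rate.** At a = 3 and c = 0:

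| b | 0.1 | 0.2 | 0.3 | 0.4 |
|---|---|---|---|---|
| AUC | 137.4 | 100.8 | 74.6 | 55.7 |

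The two influences cannot be separated from the area alone. An AUC of 74.6 arises from b = 0.1 with a = 1.63 and equally from b = 0.5 with a = 5.31.

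**Step 3: execution error, adaptation held fixed (a = 3, b = 0.3).** A constant c adds c × 63 to the area.

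| c (cm) | AUC | Change from c = 0 | SumErr | Exponent from a pure power fit |
|---|---|---|---|---|
| 0 | 74.6 | – | 76.5 | 0.30 |
| 0.5 | 106.1 | +42% | 108.5 | 0.22 |
| 1.0 | 137.6 | +85% | 140.5 | 0.17 |
| 1.5 | 169.1 | +127% | 172.5 | 0.14 |

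**Step 4: the pre/post contrast.** If treatment lowers c from 1.0 to 0.5 cm and leaves adaptation alone, AUC falls by 137.6 − 106.1 = 31.5, or 31.5/137.6 = 23%. A true gain in rate from b = 0.2 to 0.3 at a = 3 lowers AUC by 100.8 − 74.6 = 26.2, whatever the value of c. The change in arm control alone produces the larger fall.

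**Step 5: does referencing help?** Subtracting c from each trial returns AUC to 74.6 for every c in the table. The exponent of an unreferenced power fit is no cure, since the last column shows it drifting from 0.30 to 0.14.

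**The case against.** The strongest reply is that the trial compares randomised groups on change from baseline, so stable differences between patients in error level do not bias the contrast on average. That is right, and a ranking of two patients at one visit would prove little. It does not cover a treatment effect on execution error itself, which is the case in step 4.

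Second, only AUC is labelled as adaptation. SumErr is labelled accuracy and the coefficient of variation variability, and the section also presents the set as measuring motor performance. SumErr moving with arm control fits its label. The difficulty comes when it is read as evidence on adaptation.

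Third, these are secondary measures in a self-described exploratory pilot, and the links to FMA are exploratory correlations. That limits the consequence, although the Discussion does speak of verifying mediation.

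A reader might also infer more than the article supports:

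- *That the metrics do not measure adaptation.* Step 2 contradicts this: AUC falls steeply as b rises.
- *That SumErr rewards patients with fewer usable trials.* The block is fixed at 64 trials and nothing in the article drops any. A timed-out trial can still have a peak velocity. With all 64 scored, SumErr is 64 times the mean error. Handling of failed trials may sit in the full protocol.
- *That the plateau definition or the coefficient of variation is wrong.* The plateau wording is loose, but it can be read as the levelling-off of the learning curve. A fixed window, or a standard deviation instead, would be a matter of preference.

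**Conclusion.** The point holds in limited form. The label on AUC is incorrect: the area depends on rate and on error level, and without the familiarisation block as reference the listed metrics cannot separate better adaptation from better general arm control. Randomisation does not remove this, because general arm control is itself what treatment may change. Secondary objective 2 and the mediation reading are weakened; the primary FMA-UE analysis is untouched. It should be corrected, but it does not threaten the trial.

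That AUC is proportional to a under a power curve needs no assumed values. The sizes do: the twofold gap, the 42% to 127% and the 23% rest on the assumed a, b and c. They also assume that the fitted learning values are error-type scores and that execution error adds to adaptation error. The article does not define those values, and its mention of time-to-target leaves the fitted variable unclear. If time were fitted, a general gain in paretic-limb speed would raise the same problem.

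**What to change.** Reference the adaptation block to each patient's mean familiarisation-block error at the same visit. This can be done by subtraction, or by fitting c + a × t^(-b) by nonlinear least squares with c fixed at that mean. The second form is safer: after subtraction, late-trial values can reach zero or below, and a log-linear power fit cannot take them. Report b from the referenced model as the adaptation rate. Keep AUC, described as total error, and state which variable the learning curve is fitted to. Fix these definitions before the group codes are broken.

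The data are already recorded and a power fit is already planned, so the cost is a little more analysis work and some noise from estimating the familiarisation mean. With 32 independent trials, the standard error of that mean is 1/√32 = 0.18 of the trial-to-trial standard deviation.
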